## Abstract

**Background:**

The anterior cruciate ligament (ACL) is one of four major ligaments in the knee that provide stability during physical activity. A tear in the ACL is characterized by joint instability that leads to decreased activity, knee dysfunction, reduced quality of life and a loss of muscle mass and strength. While rehabilitation is the standard-of-care for return to daily function, additional surgical reconstruction can provide individuals with an opportunity to return to sports and strenuous physical activity. Over 200,000 ACL reconstructions are performed in the United States each year, and rehabilitation following surgery is slow and expensive. One possible method to improve the recovery process is the use of intramuscular testosterone, which has been shown to increase muscle mass and strength independent of exercise. With short-term use of supraphysiologic doses of testosterone, we hope to reduce loss of muscle mass and strength and minimize loss of physical function following ACL reconstruction compared to standard-of-care alone.

**Methods/design:**

This study is a double-blinded randomized control trial. Men 18–50 years of age, scheduled for ACL reconstruction are randomized into two groups. Participants randomized to the testosterone group receive intramuscular testosterone administration once per week for 8 weeks starting 2 weeks prior to surgery. Participants randomized to the control group receive a saline placebo intramuscularly instead of testosterone. Lean mass, muscle strength and physical function are measured at 5 time points: 2 weeks pre-surgery, 1 day pre-surgery, and 6, 12, 24 weeks post-surgery. Both groups follow standard-of-care rehabilitation protocol.

**Discussion:**

We believe that testosterone therapy will help reduce the loss of muscle mass and strength experienced after ACL injury and reconstruction. Hopefully this will provide a way to shorten the rehabilitation necessary following ACL reconstruction. If successful, testosterone therapy may also be used for other injuries involving trauma and muscle atrophy.

**Trial registration:**

NTC01595581, Registration: May 8, 2012

## Background

The anterior cruciate ligament is one of four major ligaments in the knee and provides stability during physical activity. A tear in the ligament is characterized by joint instability that leads to decreased activity, knee dysfunction, and reduced quality of life [1]. The initial knee injury is associated with rapid loss of muscle mass and strength, which can be regained with structured rehabilitation [1]. While rehabilitation is the standard-of-care for return to daily function, additional surgical reconstruction can provide individuals with an opportunity to return to sports and strenuous physical activity [2]. However, surgery will initially add more trauma to the knee and prolong rehabilitation. Together, these components can lead to a slow and expensive recovery [3]. Because there are at least 200,000 anterior cruciate ligament (ACL) reconstructions performed each year in the United States [1], it will be beneficial to improve the recovery process. One possible method may be the use of intramuscular testosterone, which has been shown to increase muscle mass and strength independent of exercise [4, 5]. Inducing an anabolic environment with a short course of testosterone may be an efficient method to improve recovery.

Muscle mass is dependent on the ratio of muscle protein synthesis (anabolism) to muscle protein breakdown (catabolism). Trauma from surgery and limited movement of the knee result in atrophy and breakdown due to a catabolic state and reduced anabolism of skeletal muscle proteins. Furthermore, ACL injuries can result in weeks of immobilization of the knee, and animal studies have shown that anabolism decreases after as few as 6 hours of cast immobilization [6]. The combination of surgery, the initial knee injury, and the associated limited movement contribute to the delayed and intensive rehabilitative process.

Testosterone increases myofibrillar protein synthesis and promotes anabolism of muscle tissue. It also modulates the activity of immune, fibroblast, and myogenic precursor cells, which are all involved in muscle regeneration. Furthermore, testosterone administration increases lean tissue and maximal voluntary strength in a dose-dependent manner [5]. Animal models have shown that exogenous testosterone aids in muscle regeneration following several types of injury, such as crush injuries, venom-induced muscle injury, muscle disuse atrophy, and injury following muscle graft surgery [7]. With testosterone, successful regeneration of healthy mouse muscle can occur within 2–3 weeks of injury where muscle strength can return to pre-injured values [7].

Testosterone may also induce muscle growth via growth hormone (GH) and insulin-like growth factor 1 (IGF-1) [7, 8]. IGF-1 can stimulate muscle protein synthesis and satellite cell activity and anabolic steroids increase both circulating IGF-1 and muscle mRNA expression of *IGF*-*1*. Akt (protein kinase B) is a signaling mediator of IGF-1 that can regulate muscle mass. However, it is also known that testosterone can work outside of the Akt signaling pathway in order to maintain skeletal muscle hypertrophy [7, 9]. We are studying key regulatory proteins such as Akt1, mTOR, and FOXO3a, which have not been studied in concurrent states of muscle trauma and testosterone administration.

There is evidence that the Akt pathway regulates gene transcription through the inactivation of a group of transcription factors (FOXOs) located in the nucleus [10, 11]. FOXO3a increases the transcription of atrophy related genes (atrogens), decreases protein degradation, and results in muscle atrophy. Phosphorylation of FOXO3a by phosphorylated Akt1 inactivates the transcription factor, releasing it from DNA and resulting in translocation of the inactive FOXO3a to the cytosol [11]. Phosphorylated Akt1 will also activate the mTOR pathway to stimulate protein synthesis and result in hypertrophy [11]. Therefore, the Akt pathway may regulate both skeletal muscle protein synthesis and degradation by different but complimentary mechanisms in response to testosterone (Figure 1). By analyzing muscle tissue following an ACL rupture with or without testosterone administration, we can learn more about the mechanism through which muscle adapts to trauma and how testosterone affects this process. Therefore, we may learn more about testosterone’s mechanism of action in skeletal muscle during the catabolic stimulus of bedrest and surgery.

**Figure 1 Fig1:**
[figure not shown]
**Akt1 signaling and control of skeletal muscle hypertrophy and atrophy.** Anabolic signals (e.g. testosterone) initiate phosphorylation (P) of Akt1, which activates protein synthesis via the mTOR pathway. At the same time, Akt1(P) inactivates FOXO3a by phosphorylation and facilitates translocation of FOXO3a out of the nucleus, resulting in inhibition of the atrophy-related genes (atrogens), and thereby decreasing protein degradation. On the other hand, catabolic stimuli (e.g. glucocorticoids) dephosphorylate and thereby inactivate the Akt1 protein. Inactivation of the Akt1 protein allows expression of *FOXO3a* in the nucleus and subsequent activation of the atrogens, resulting in protein degradation. (Figure adapted from G.A. Nader) [10].

In addition to understanding the possible mechanisms of testosterone, there may be improved recovery time as measured by questionnaires and function tests. In a study using the Tegner Activity Scale [12], a questionnaire developed to describe a patient’s physical activity, 60% of participants who received ACL reconstruction did not return to pre-injury activity level within 2 years [1]. In another study where supraphysiologic doses of testosterone were given to older men undergoing knee replacement, the physical function as measured by the Functional Independence Measure ability to stand was significantly higher by 30% in patients who received testosterone. Similarly, we hope to improve recovery following ACL reconstruction using supraphysiologic doses of testosterone. Specifically, we hope to reduce the loss of muscle mass and strength and minimize loss of physical function. Should acute testosterone improve rehabilitation following ACL surgery, it may be possible to apply the same concept to other injuries that involve muscle atrophy.

### Objectives

The overall objective of this study is to determine if 8 weeks of testosterone first administered 2 weeks prior to surgery, can improve the outcome of ACL reconstruction. Specifically, we will evaluate the effect of testosterone administration on lean muscle mass and strength, physical function, clinical outcomes, and skeletal muscle myogenic regulators following ACL reconstructive surgery. We hypothesize that testosterone will minimize the reductions or potentially increase muscle mass and strength following surgery and may hasten a patient’s return to physical activity. If testosterone improves recovery after ACL surgery, the same treatment may be used for other injuries that involve trauma and muscle atrophy. Furthermore, this study will examine the effect of trauma with or without testosterone on myogenic regulators in muscle tissue taken during ACL surgery—providing possible mechanistic insights for the clinical outcomes.

## Methods

### Study design

Men, 18–50 years of age, scheduled for ACL reconstructive surgery will be randomized to one of two groups. Although most ACL tears occur in women [2], this study will be limited to men due to the gender-related side effects of testosterone. According to our power analysis, we aim to have at least 7 patients in each group after recruiting and screening approximately 70 patients. The dosing is based on a previous study using supraphysiological dose of testosterone for knee replacement surgery [13]. Intramuscular testosterone cypionate will be used because it has been more widely studied and is less expensive than the gel or patch forms of testosterone. Group 1 will receive testosterone administration, one weekly 200 mg dose intramuscularly of testosterone in sesame oil, for 8 continuous weeks beginning 2 weeks prior to surgery and standard-of-care rehabilitation following surgery. Group 2 will follow the same dosing and rehabilitation schedule but receive a saline placebo instead of testosterone. The dose will be given intramuscularly to minimize systemic side effects; however, we expect the total systemic levels of testosterone to increase to an average of 1200 ng/dl. Lean mass, muscle strength, and physical function will be measured 2 weeks prior to surgery, 1 day prior to surgery, and 6, 12, and 24 weeks following surgery. By administering the dose 2 weeks prior to surgery, there will be sufficient time to develop an anabolic state before the catabolic stimulus of surgery. The dose will continue for 8 weeks to try to maintain muscle mass when there is limited movement and endogenous anabolic stimulus. After 6 weeks from the surgery, testosterone will no longer be administered because KOOS function and sports score appear to stabilize after this time [1]. The study will be a double-blinded experiment.

Patients will follow a standard rehabilitation protocol [14] customized by an orthopedic physician. Rehabilitation will begin shortly after surgery and will be supervised by a licensed physical therapist. The protocol includes goals for range of motion, muscle function, and functional performance at different post-operative stages. The goals for each stage must be met before patient progresses to the next stage and the amount of exercises will be closely monitored by physical therapists and the graduate student. A quicker progression is expected in patients assigned to standard-of-care rehabilitation with testosterone. If any pain or swelling slows progression, the patient will see the treating clinician.

The study will be conducted at the University of Southern California (USC), Keck School of Medicine in Los Angeles, California and was approved by the Institutional Review Board of the University of California (HS-11-00649).

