### Selection and randomization of subjects

Male participants, 18–50 years of age, who present to the orthopedic surgeon with recent knee trauma will be screened for eligibility. Eligible patients will have had rotational trauma to a previously uninjured knee within the preceding 8 months, ACL insufficiency as determined by clinical examination (positive pivot shift and/or positive Lachmann test), and a score of 5 to 9 on the Tegner Activity Scale (TAS) [12] before the injury (scores range from 1 to 10, with a score of 5 indicating participation in recreation sports, and a score of 9 indicating participation in competitive sports on a nonprofessional level).

All eligible participants (see Table 1) will receive information about the trial orally and in writing. After signing a written informed consent, they will be randomly assigned to undergo either standard-of-care structured rehabilitation with testosterone administration or standard-of-care structured rehabilitation with placebo. An investigator not involved in the randomization procedure will prepare sequentially numbered, opaque, sealed envelopes containing the assigned interventions to ensure randomness which will then be provided to the research pharmacist. The study is a double blind study. Only the research pharmacist will know which patient is receiving study drug or placebo. The surgeon, PI, study team, and physical therapist will not know which study arm the patient was randomized. The protocol for rehabilitation will remain the same for all patients.

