### Study agent administration and safety

Although the study involves a very short course of testosterone, it may still have side effects on the endocrine systems; and therefore, common markers of endocrine function are monitored. Blood analysis will be performed at USC. Pituitary hormones (LH and FSH), prostate-specific antigen (PSA), liver enzymes, hematocrit, and blood pressure are measured at two weeks preoperatively, 1 day preoperatively, and 2, 3, 6, 12, and 24 weeks postoperatively.

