#### Drug delivery

Either testosterone or placebo will be injected intramuscularly once per week for 8 weeks, starting 2 weeks prior to surgery and ending 5 weeks post-surgery.

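### Testosterone in sesame oil is compared with a saline placebo, so the claimed double blind is not secured as described, chiefly for whoever prepares or gives the injections

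*Protocol article*

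**What the plan says.** All places are in the protocol article.

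- **Active injection** (Study design): "one weekly 200 mg dose intramuscularly of testosterone in sesame oil".
- **Control injection** (Study design): "Group 2 will follow the same dosing and rehabilitation schedule but receive a saline placebo instead of testosterone". The abstract repeats it: "Participants randomized to the control group receive a saline placebo intramuscularly instead of testosterone".
- **Exposure** (Drug delivery): "Either testosterone or placebo will be injected intramuscularly once per week for 8 weeks". The study calendar (Table 2) marks eight deliveries, the last 5 weeks after surgery.
- **Blinding claim**: the abstract, Study design, and Selection and randomization of subjects all call the trial double-blind. The last of these says "Only the research pharmacist will know which patient is receiving study drug or placebo" and lists the surgeon, the principal investigator, the study team and the physical therapist as blinded.
- **Allocation envelopes** (same section): "An investigator not involved in the randomization procedure will prepare sequentially numbered, opaque, sealed envelopes containing the assigned interventions to ensure randomness". The envelopes then go to the research pharmacist.
- **Laboratory monitoring** (Study agent administration and safety): "Pituitary hormones (LH and FSH), prostate-specific antigen (PSA), liver enzymes, hematocrit, and blood pressure are measured" at seven times: 2 weeks and 1 day before surgery, and 2, 3, 6, 12 and 24 weeks after it.

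**The concern.** A placebo supports a blind only if it cannot be told from the drug by the people who handle it. An oil solution and a watery one look different in the syringe and flow differently through the needle. The mismatch is a design choice written into the article. It is not a pharmacy detail left to a fuller document.

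If the arm becomes known or guessed, four measures are open to expectation or judgement:

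- maximal strength on the dynamometer, which depends on effort and encouragement;
- KOOS, which is self-reported;
- the Tegner scale, which is also self-reported;
- progression through rehabilitation stages, which therapists monitor. The Study design section already states that faster progression is expected on testosterone.

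Strength matters most here. It stands beside lean mass in the ANCOVA of the Statistical data analysis section, and it supplies one of the two effect sizes in the Power analysis. No later analysis can undo bias that entered through a lost blind.

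**Working it through.** **1. The preparations side by side**

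| | Active arm | Control arm |
|---|---|---|
| Liquid | sesame oil | saline |
| Route | intramuscular | intramuscular |
| Schedule | weekly, 8 injections | weekly, 8 injections |

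Route and schedule match; the liquid does not. The person drawing up or injecting meets the difference directly and, if that person serves both arms, can compare the two. A participant meets only one of the two liquids.

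**2. Exposure of each outcome**

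| Outcome | Section | Open to expectation? |
|---|---|---|
| Maximal strength | Physical function tests | Yes, by effort |
| KOOS, Tegner scale | Questionnaires | Yes, by self-report |
| Rehabilitation progression | Study design | Yes, by judgement; no analysis of it is listed |
| Lean mass by DXA | Body composition testing by DXA | Little |
| Gene expression | Muscle biopsies | Little |

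**3. The plan's own sample size**

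Inputs from the Power analysis: α = 0.05, power 0.80, effect sizes 2.0 (mass) and 2.03 (strength), minimum 6 per group, 7 enrolled. Sidedness is not stated; I take it as two-sided.

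For n per arm and standardised difference d, the t statistic has 2n − 2 degrees of freedom and noncentrality d × √(n/2). At d = 2.0 the power is 0.79 with 5 per group and 0.88 with 6, so the stated minimum of 6 is reproduced. At d = 2.03 the figures are 0.80 and 0.89.

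**4. Illustration of what lost blinding could do**

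The same function is used, with no true drug effect and a shift of b SD in favour of testosterone. With 7 per arm there are 12 degrees of freedom and the two-sided 5% critical value is 2.179. The noncentrality is b × √3.5 = 1.871b.

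| Assumed b (SD) | Noncentrality | Significant, 7 per arm | Significant, 5 per arm |
|---|---|---|---|
| 0 | 0 | 5% | 5% |
| 0.25 | 0.468 | 7.2% | 6.4% |
| 0.5 | 0.935 | 13.9% | 10.8% |
| 1.0 | 1.871 | 40.6% | 28.6% |

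The values of b are assumptions; the article gives no size for such a shift. The table uses a plain two-sample t-test, as a simple stand-in for the planned ANCOVA.

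**5. Who knows the allocation**

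One sentence reserves knowledge of each patient's arm to the pharmacist. Another has an investigator fill numbered envelopes with the assignments. Whoever fills them has seen the sequence, although not necessarily which patient took which number. The same person is described as uninvolved in randomization, while doing part of it.

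**6. Hormone values**

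Dosing runs from 2 weeks before to 5 weeks after surgery. Of the seven LH/FSH time points, the draws at 1 day before surgery and at 2 and 3 weeks after it fall between the first and last injections. Exogenous testosterone suppresses both hormones, so these values could reveal the arm to anyone who sees them. The article does not say who does.

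**The case against.** A reader might infer that the blind cannot hold at all. The article does not support that. It does not say who draws up or gives the injections, or whether syringes are masked, and such detail may sit in a full protocol that is not shown. An unblinded injector with no other trial role would contain much of the problem. This stands, and it limits the claim to a blind that is not secured as described. It does not remove the point, because masking arrangements would not make saline match oil.

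A reader might also infer that participants will often recognise their injection. This is a parallel-group trial and each man receives one preparation only, so he has nothing to compare it with. That objection stands too; the injector is the main route.

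The envelope wording is weaker than a full contradiction. Knowing a sequence is not knowing which patient has which arm, and the article does not say that this investigator enrols, treats or assesses anyone. It remains an unclear passage about concealment. It is not evidence of biased outcomes.

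The LH/FSH point depends on who reads the results, which is not stated. The rejection rates measure the assumed shift and not this trial. It would also be too strong to say that drug effect and expectation cannot be separated on any outcome, since DXA lean mass and gene expression are little open to expectation.

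**Conclusion.** The point holds in limited form. The article commits to a placebo that does not match the drug's vehicle while claiming a double blind. The blind is therefore not secured as described for strength, KOOS, the Tegner scale and rehabilitation progression. Lean mass by DXA and gene expression are much less affected.

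The bias has no known size. The rates of about 7%, 14% and 41% at 7 per arm rest entirely on assumed shifts of 0.25, 0.5 and 1.0 SD, a two-sided 5% t-test and no true drug effect. They show only that a modest shift does limited harm and a large one does serious harm. The envelope wording and the hormone results are secondary. This should be fixed before dosing begins, but it does not by itself invalidate the trial, and no sample-size figure changes.

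**What to change.** **Main change.** Use the drug's oil vehicle without testosterone as the placebo, and say so in the Study design and Drug delivery sections and in the abstract. The cost is sourcing a vehicle placebo, which the article does not price, and controls then receive oil injections. Sleeved syringes alone are not enough, because they hide appearance but not viscosity.

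**Secondary changes.**

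1. Reconcile the two statements on allocation in Selection and randomization of subjects. One way is for the research pharmacist, who is already unblinded, to prepare and hold the sequence, so that no investigator fills envelopes. This needs only a change of task.
2. Keep on-treatment LH and FSH values from staff who treat or assess patients. Because they are safety measurements, name someone outside those roles to review them and act on abnormal values. The cost is that reviewer's time.

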#### Questionnaires

The subject will be asked to complete the Knee Injury and Osteoarthritis Outcome Score [32, 33] (KOOS), a commonly used test to measure progression after ACL reconstruction, and the Tegner Activity Scale [12, 34–37] to determine physical activity level.

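### An oil-based testosterone injection is compared with a saline placebo, so the products as described do not secure the stated double blind

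*Protocol article*

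**What the plan says.** The Study design section of the protocol article describes the active treatment as "one weekly 200 mg dose intramuscularly of testosterone in sesame oil", and the control arm as follows: "Group 2 will follow the same dosing and rehabilitation schedule but receive a saline placebo instead of testosterone". The Methods/design paragraph of the abstract also names saline: "Participants randomized to the control group receive a saline placebo intramuscularly instead of testosterone".

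On blinding, Study design says: "The study will be a double-blinded experiment". Selection and randomization of subjects says who may know the arm: "Only the research pharmacist will know which patient is receiving study drug or placebo". It then says who may not: "The surgeon, PI, study team, and physical therapist will not know which study arm the patient was randomized".

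The Drug delivery section sets the frequency: "Either testosterone or placebo will be injected intramuscularly once per week for 8 weeks". Table 2 agrees, with eight rows marked for drug delivery. Neither place says who gives the injection.

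**The concern.** The two injections are different kinds of liquid. One is an oil solution and the other is aqueous, so they are likely to look different in the syringe and to need different force to inject. The article promises that one person alone knows the arm, yet the contents of the syringe may reveal it to anyone who handles or sees it.

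The stakes depend on the outcome. Maximal strength on the Cybex dynamometer depends on effort. KOOS and the Tegner scale are reported by the participant ("The subject will be asked to complete the Knee Injury and Osteoarthritis Outcome Score"). If a participant or an assessor knows the arm, these can move without any drug effect. There is also a route through treatment. The Study design section says that quicker progress through rehabilitation is expected on testosterone, and physical therapists monitor progress from stage to stage. A therapist who learned the arm could change the rehabilitation that is delivered. No later analysis can restore a blind once it is lost.

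**Working it through.** The protocol gives no figure on blinding to reproduce. The check is a comparison of what the article states, followed by an illustrative calculation.

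**Comparison of the text**

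1. Vehicles: sesame oil in the active arm (Study design); saline in the control arm (Study design and abstract). The mismatch is stated in both arms' descriptions and is not something the article leaves out.
2. Who may know: the research pharmacist alone. If the pharmacist fills the syringes, that step breaches nothing.
3. Who must not know: the surgeon, PI, study team and physical therapist, and, under a double blind, the participant.
4. Concealment: the opaque sealed envelopes in Selection and randomization of subjects hide the allocation sequence. They do nothing to hide the product in the syringe.
5. Timing: in Table 2 the first injection falls at the visit 2 weeks before surgery. The four later assessments (1 day before surgery, and 6, 12 and 24 weeks after) all follow at least one injection. At the visits 2 weeks and 1 day before surgery, injection, function testing and questionnaires share the same visit.
6. Exposed outcomes among those analysed in Statistical data analysis: strength, KOOS and Tegner. Lean mass by DXA and gene expression by q-PCR come from instruments and are much less exposed.

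**Illustration of size**

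Inputs: 7 per arm (planned) and 6 per arm (stated minimum), both from Power analysis; two-sided α = 0.05, with α from Statistical data analysis. The bias shift d, in SD units, is an assumption, because the documents give none.

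Suppose that testosterone has no effect and that knowledge of the arm adds a difference d between the arms. For an unadjusted two-sample t-test with n per arm, the degrees of freedom are 2n − 2 and the noncentrality is d × √(n/2). The rejection probability is P(|T| > t_crit) under the noncentral t distribution.

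- n = 7: df = 12, t_crit = 2.179, √(7/2) = 1.871.
- n = 6: df = 10, t_crit = 2.228, √(6/2) = 1.732.

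| Assumed shift d | Noncentrality, n = 7 | Rejection, n = 7 | Noncentrality, n = 6 | Rejection, n = 6 |
|---|---|---|---|---|
| 0 | 0 | 5.0% | 0 | 5.0% |
| 0.25 | 0.468 | 7.2% | 0.433 | 6.8% |
| 0.50 | 0.935 | 13.9% | 0.866 | 12.3% |
| 0.75 | 1.403 | 25.3% | 1.299 | 21.8% |

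The planned analysis is ANCOVA adjusted for baseline, so the t-test is only an approximation to it.

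**The case against.** The strongest reply is that different vehicles do not prove that anyone was unblinded. The article does not say who injects. The full protocol is not shown, and it may provide for masked syringes or for an injector with no other role; a condensed article commonly leaves such detail out. Assessors and therapists who never see an injection could stay blind. Each participant receives only one product and never compares the two, so eight injections are not eight independent chances for him to identify it.

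All of this stands, and it limits the claim. A reader might infer that the double blind has failed, or that the injector belongs to the blinded study team. The article supports neither.

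A reader might also infer that expectation alone could produce the whole hypothesised benefit. That goes too far: the hypothesis includes muscle mass, which is measured by instrument, and stage-by-stage progression is not an analysed outcome. Nor does anything in the article suggest that the oil itself affects mass, strength or KOOS.

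The mismatch in the products remains. Even if a masked syringe hides the appearance, the difference in resistance would still reach the injector. An independent injector would protect the assessors, but the participant would still receive a different kind of injection according to arm.

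**Conclusion.** The point holds in a limited form. The article states a placebo whose vehicle does not match the active product, and it promises a blind that this pairing does not secure for the injector or for a participant or staff member who sees the injection. That an oil solution and saline can be told apart is inferred from the stated vehicles; the article does not say so.

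The exposure falls on Cybex strength, KOOS and Tegner. DXA lean mass and gene expression are much less affected, except that lean mass could be reached indirectly if therapists learned the arm and changed rehabilitation.

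The size of any bias is unknown. Over the assumed range of 0.25 to 0.75 SD, the false-positive rate at 7 per arm runs from 7% to 25%. The low end is close to nominal and the high end is five times the stated 5%. These figures assume that the whole shift appears as a difference between the arms. The finding itself does not depend on them.

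**What to change.** Replace the saline placebo with drug-free sesame-oil vehicle, matched to the active product in volume and appearance. The research pharmacist, who already knows the allocation, dispenses both in identical opaque-sleeved syringes. Sleeves alone, with saline kept, would not be enough, because the difference in resistance would remain. Any safety implication of giving the vehicle to control participants is for the investigators to judge.

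Record participants' and assessors' guesses of the arm, so that the blind can be described in the report. If men have already received saline, report their strength, KOOS and Tegner results as not reliably blinded.

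The cost is a protocol amendment and pharmacy supply of vehicle for about 7 men × 8 injections = 56 injections. The downside is that placebo participants receive an oil injection.
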